**10.6. Sample Size Determination**

Due to the absence of prior studies using a similar methodology, the present study will be conducted as a pilot involving 10 participants. Based on the outcomes obtained from this initial sample, the final sample size will be calculated. Ultimately, the number of participants will be determined according to the available sample pool and the time constraints of the study.

**10.7. Study Procedures**

In this study, adult male athletes with a history of unilateral ACLR using hamstring autografts will be recruited through public announcements posted in physiotherapy clinics, outpatient centers, hospitals across Isfahan, and digital outreach via social media platforms. Participants will be selected using a non-random, convenience sampling method, based on predefined inclusion and exclusion criteria. Notably, only athletes who underwent ACLR using hamstring autografts and whose surgeries were performed using a standardized surgical technique will be eligible.

Eligible individuals will be enrolled in the study after completing an informed consent form approved by the Ethics Committee of Shahid Beheshti University of Medical Sciences. Participants will then be randomly assigned to either the intervention group or the sham stimulation group.

Prior to the start of the intervention, all participants will complete a demographic questionnaire, as well as the IKDC, ACL-RSI, and KOOS questionnaires. Pain levels will also be assessed using the VAS.

**ACL-RSI Questionnaire**

The ACL-RSI questionnaire is a psychological assessment tool designed to evaluate the mental readiness of athletes returning to sport following ACL injury ([69](#_ENREF_69)). Developed by Webster et al., this scale measures how psychological factors—including emotional responses, confidence in performance, and risk appraisal—affect an athlete’s return-to-sport decision-making. It is widely used as a predictive indicator of psychological readiness in athletes recovering from ACL injury ([96](#_ENREF_96)).

The ACL-RSI is a 12-item questionnaire, with each item rated on an 11-point scale. The instrument comprises three subdomains: (1) emotions (5 items), (2) confidence in performance (5 items), and (3) risk appraisal (2 items). The total score is calculated as a percentage of the maximum possible score across all 12 items. Higher percentage scores indicate greater psychological readiness to return to sport ([96](#_ENREF_96)).

In the present study, the Persian version of the ACL-RSI questionnaire will be used ([69](#_ENREF_69)) (Appendix 5).

**International Knee Documentation Committee (IKDC) Questionnaire**

The IKDC questionnaire is a patient-reported outcome measure specifically designed to assess knee-related clinical symptoms. It includes items related to pain intensity, daily functional activities, and overall knee performance. The instrument consists of 18 items divided into three subscales: (1) clinical symptoms (items 1–7), (2) sports activity function (items 8–17), and (3) overall knee function (item 18).

The questionnaire evaluates clinical symptoms such as pain, stiffness, swelling, joint locking, and instability, as well as functional abilities including running, jumping and landing, sudden stopping, stair navigation, standing, kneeling, sitting with a flexed knee, and rising from a chair. Scores range from 0 to 100, with higher scores indicating better functional status and milder clinical symptoms. A score of 100 reflects full participation in sports without any clinical limitations, while a score of 0 indicates severe impairment and maximal symptom burden ([97](#_ENREF_97)).

The reliability and validity of the Persian version of the IKDC questionnaire have been confirmed in ACLR patients. In the present study, the validated Persian version developed by Rahimi will be used ([98](#_ENREF_98)).

**Knee Injury and Osteoarthritis Outcome Score (KOOS)**

The KOOS questionnaire is composed of multiple subdomains, with pain and functional ability being two of its core components. In the Persian-adapted version of KOOS, pain is assessed through nine specific items. Each item is scored on a 5-point Likert scale ranging from 0 to 4, where 0 = none, 1 = mild, 2 = moderate, 3 = severe, and 4 = extreme.

Pain scoring is calculated using the average of the scores from the nine pain-related items (P1–P9), according to the standardized formula. Higher scores indicate greater levels of perceived pain ([99](#_ENREF_99)).

[figure not shown]

**Functional Assessment in the KOOS Questionnaire**

In the Persian-adapted version of the KOOS (Knee Injury and Osteoarthritis Outcome Score), physical function is evaluated using 17 items that cover a wide range of daily activities, such as stair climbing, rising from a seated position, and other routine movements. In addition to the daily living subscale, the questionnaire includes a sport and recreation subscale comprising five items, and a quality-of-life subscale consisting of four items.

Each item is scored on a 5-point Likert scale ranging from 0 to 4, where 0 = none, 1 = mild, 2 = moderate, 3 = severe, and 4 = extreme. The functional score is calculated using a standardized formula based on the average score across relevant items. Higher scores indicate poorer functional performance ([99](#_ENREF_99)).

ADL= Activity Daily Living, SPORT/REC= Sport/Recreation, QOL= Quality of Life

In the present study, the Persian-adapted version of the KOOS questionnaire will be used ([99](#_ENREF_99)).

**Visual Analog Scale (VAS)**

The Visual Analog Scale (VAS) is one of the most widely used tools for assessing pain intensity in clinical research. It consists of a horizontal line measuring 100 millimeters in length, where the left end (0 mm) represents "no pain" and the right end (100 mm) indicates "maximum pain intensity." Prior to treatment, participants are asked to mark the point on the line that best reflects the highest level of pain they have experienced ([100](#_ENREF_100)).

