7.2. Specific Descriptive Objectives

1. To determine KOOS questionnaire scores in the intervention and control groups before and after tDCS.

2. To determine IKDC questionnaire scores in the intervention and control groups before and after tDCS.

3. To determine ACL-RSI questionnaire scores in the intervention and control groups before and after tDCS.

4. To determine pain levels using the VAS in the intervention and control groups before and after tDCS.

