7.3. Specific Analytical Objectives

1. To compare the effect of motor cortex a-tDCS with sham tDCS on quadriceps strength in individuals post-ACLR, relative to the control group, before and after stimulation.

2. To compare quadriceps muscle strength in ACLR individuals before and after motor cortex stimulation with tDCS.

3. To compare central activation ratio to quantify quadriceps activation failure before and after motor cortex stimulation with tDCS.

4. To assess the correlation between a-tDCS parameters and total KOOS scores and domain scores in the intervention and control groups before and after tDCS.

5. To assess the correlation between a-tDCS and IKDC questionnaire scores in the intervention and control groups before and after tDCS.

6. To assess the correlation between a-tDCS and ACL-RSI questionnaire scores in the intervention and control groups before and after tDCS.

7. To assess the correlation between a-tDCS and VAS-reported pain scores in the intervention and control groups before and after tDCS.

8. To compare KOOS questionnaire scores in the intervention and control groups before and after tDCS.

9. To compare IKDC questionnaire scores in the intervention and control groups before and after tDCS.

10. To compare ACL-RSI questionnaire scores in the intervention and control groups before and after tDCS.

11. To compare VAS pain scores in the intervention and control groups before and after tDCS.

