**Pain**

**Scientific Definition :**According to the International Association for the Study of Pain, pain is defined as an unpleasant sensory and emotional experience associated with actual or potential tissue damage, or described in terms of such damage ([89](#_ENREF_89)).

**Practical Definition:** In the present study, pain will be assessed using the VAS as well as the IKDC and KOOS questionnaires.

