**Study Design, Randomization, and Blinding**

This study will follow a parallel-group design. After completion of the pilot phase and determination of the final sample size, eligible participants will be randomly assigned to one of two groups: (1) routine physiotherapy plus a-tDCS, or (2) routine physiotherapy plus sham tDCS (s-tDCS).

Randomization will be performed by an independent individual not involved in the study, using sealed, opaque envelopes containing each participant’s identification number and assigned group (active/sham). All assessments will be conducted by the principal investigator, while tDCS (active or sham) will be administered by a separate individual who is blinded to the study details.

To ensure double-blinding, participants will remain unaware of the nature of the intervention they receive, and the assessor will be blinded to group allocation. To achieve this, tDCS stimulation and baseline physiotherapy treatment, as well as pre- and post-intervention assessments, will be conducted independently by two separate individuals.

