The average torque from the five MVIC attempts will be used to quantify quadriceps strength. This procedure will be conducted prior to the tDCS intervention to establish baseline strength values. The same protocol will be repeated following completion of ten tDCS sessions to assess post-intervention changes in muscle strength.

[figure not shown]
.
[figure not shown]

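### The VAS item asks for worst pain with no recall period and is described only at baseline, so it is unsuited to the before/after pain comparison in the objectives

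*Protocol*

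**What the plan says.** The Visual Analog Scale section of the Protocol describes a 100 mm line and then gives the rating instruction: "Prior to treatment, participants are asked to mark the point on the line that best reflects the highest level of pain they have experienced". This is the only place where the wording of the VAS question appears.

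Section 10.7 (Study Procedures) also places the VAS at baseline. It states "Prior to the start of the intervention, all participants will complete a demographic questionnaire, as well as the IKDC, ACL-RSI, and KOOS questionnaires", and the next sentence adds "Pain levels will also be assessed using the VAS".

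The objectives need two time points. Descriptive objective 4 in section 7.2 is "To determine pain levels using the VAS in the intervention and control groups before and after tDCS". Analytical objective 11 in section 7.3 is "To compare VAS pain scores in the intervention and control groups before and after tDCS". Analytical objective 7 also uses VAS scores from both time points.

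Two other passages bear on timing. The section on design, randomization and blinding says that "pre- and post-intervention assessments, will be conducted independently by two separate individuals", without listing the instruments. The strength assessment has an explicit repeat: "The same protocol will be repeated following completion of ten tDCS sessions to assess post-intervention changes in muscle strength". No matching sentence exists for the VAS.

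Pain is not left to the VAS alone. The definition of pain in section 9 says that "pain will be assessed using the VAS as well as the IKDC and KOOS questionnaires".

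**The concern.** A before/after comparison needs the same question at both visits, and that question must be able to move in both directions. The stated item asks for a maximum and sets no limit on how far back the participant should look. Section 10.3 enrols athletes two months after reconstruction, so the worst pain a participant recalls may be that of the injury or the operation. Participants may also choose different look-back periods, since none is given.

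At stake is the interpretation of the VAS objectives. A flat VAS result could come from the question and still be read as no effect on pain. The protocol has some interest in this: its literature review suggests that less pain may contribute to a strength gain.

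**Working it through.** No stated figure can be reproduced here, because the protocol gives no VAS effect, standard deviation or power. The check is to set the item against the objectives and follow each way the missing post-treatment rating could be filled.

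**Notation.** Let P be pain at any moment, M(pre) the worst pain up to baseline, M(post) the worst pain up to the end of treatment, and C a rating of current or recent pain.

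**Case 1: the same item, read without a time limit, is repeated after session 10.** The period covered at the second visit contains the period covered at the first, so

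M(post) − M(pre) = max(0, worst P during the course − M(pre)) ≥ 0.

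The change is zero unless pain during the course exceeds everything before it. Where M(pre) includes injury or surgical pain, most changes would be expected to be zero in both arms. Apart from recall or marking error, the score cannot fall, so relief is not recorded.

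**Case 2: a different item, such as current pain, is used afterwards.** The recorded change splits into two parts:

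C(post) − M(pre) = [C(post) − C(pre)] + [C(pre) − M(pre)].

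The first bracket is the change of interest. The second is zero or negative in every participant whatever the treatment, because current pain cannot exceed worst pain. Both arms would show a fall produced by the wording. With randomization the second bracket has the same expectation in both arms, so a between-group contrast is not biased on average. It does carry extra noise, and the within-group before/after changes are not interpretable.

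**Case 3: one item with a bounded window is used at both visits.** The score can rise or fall, and the two ratings measure the same thing. This is the only case that serves objectives 7.2(4) and 7.3(11) as written.

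**How long may the window be?** The Intervention Protocol gives ten sessions at four per week: 10 ÷ 4 = 2.5 weeks, or 2.5 × 7 = 17.5 days. A rating after session 10 must not reach back before treatment began, so the window has to be shorter than that. Both 24 hours (1 day) and 7 days meet this; the 7-day window leaves 17.5 − 7 = 10.5 days.

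**Is the wording fixed elsewhere?** KOOS, IKDC and ACL-RSI are used in named Persian versions and appear in the instrument list of section 10.8 with appendices. The VAS is not in that list and has no appendix. Its wording rests on the one sentence quoted.

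**The case against.** The strongest reply is that this is loose description and not a faulty measure. Apart from the quoted sentence, the VAS section describes the scale in general terms, in the present tense and with a citation, while most study procedures are written in the future tense. The form is not among the material available and may carry a sensible recall period. This lowers certainty about what participants will actually be asked. It does not remove the defect, because the protocol's only instruction is unbounded.

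A reader might infer more than the text supports:

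- *That the item asks for the worst pain ever felt.* The protocol does not say ever. It leaves the period open, and a lifetime maximum is one possible reading.
- *That pain will be rated only before treatment.* The protocol does not say only. The objectives state a VAS after stimulation, and post-intervention assessments are mentioned in general. Section 10.7 treats KOOS, IKDC and ACL-RSI in the same way, so the thin account of post-treatment timing is not peculiar to the VAS. The unbounded maximum is.
- *That the VAS has no power, or a calculable loss of power.* The protocol has no VAS standard deviation or effect, and section 10.6 leaves the final sample size to be set after a pilot of 10. Any figure would rest wholly on assumed inputs.

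It is also fair to say that a misleading VAS would not stand alone. KOOS has a nine-item pain subscale and IKDC includes pain items. Section 8 has no between-group hypothesis on the VAS, only a correlation question.

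**Conclusion.** The point holds in a limited form. The VAS item asks for worst pain with no recall period and is described only at baseline, while two objectives compare scores before and after stimulation. On a literal reading it is unsuited to showing a reduction, and changing the question afterwards would make the two ratings non-comparable.

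That it could not show any fall rests on two assumptions: that participants take the item as unbounded, and that they recall and mark consistently. If the form already sets a short window and is used at both visits, the defect is confined to the protocol text.

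The size is modest and cannot be given as a number from this document. VAS pain is secondary to quadriceps strength and other instruments cover pain, so the main comparison is untouched. It still merits correction, because an analysis plan cannot restore a recall window that participants were never given.

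**What to change.** Replace the rating sentence in the Visual Analog Scale section with one question that has a stated recall window shorter than the roughly 2.5-week course, for example worst knee pain in the past 24 hours or in the past 7 days. State that the identical question is given before treatment and again after session 10, and print it on the form.

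The cost is one sentence and a form change, with no new visit. It should be done before the first baseline rating, since a baseline taken with an unsuitable question cannot be recovered later.

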**Study Design, Randomization, and Blinding**

This study will follow a parallel-group design. After completion of the pilot phase and determination of the final sample size, eligible participants will be randomly assigned to one of two groups: (1) routine physiotherapy plus a-tDCS, or (2) routine physiotherapy plus sham tDCS (s-tDCS).

Randomization will be performed by an independent individual not involved in the study, using sealed, opaque envelopes containing each participant’s identification number and assigned group (active/sham). All assessments will be conducted by the principal investigator, while tDCS (active or sham) will be administered by a separate individual who is blinded to the study details.

To ensure double-blinding, participants will remain unaware of the nature of the intervention they receive, and the assessor will be blinded to group allocation. To achieve this, tDCS stimulation and baseline physiotherapy treatment, as well as pre- and post-intervention assessments, will be conducted independently by two separate individuals.

## Procedure

## The intervention protocol will be implemented according to the flowchart outlined below for both groups: routine physiotherapy combined with a-tDCS and routine physiotherapy combined with sham tDCS (s-tDCS).

**Quadriceps Strength Assessment Using a Dynamometer**

Quadriceps muscle strength will be measured using a dynamometer (Figure 5), a device widely utilized in previous studies ([36](#_ENREF_36), [39](#_ENREF_39), [51](#_ENREF_51)). The dynamometer enables the research team to evaluate maximal voluntary isometric contractions (MVIC) of the quadriceps muscle before and after tDCS intervention in athletes with ACLR.

Initially, isometric strength will be assessed by collecting the peak voluntary force generated by the quadriceps muscle. Participants will first perform a 5-minute warm-up on an ergometric bicycle. They will then be seated on the dynamometer with the hip and knee joints positioned at approximately 90 degrees of flexion. Stabilization straps will be secured around the waist and shoulders to minimize extraneous movement during knee extension.

The tibia will be positioned just above the ankle joint—approximately 5 cm proximal to the lateral malleolus—on the anterior surface of the lower limb, and fastened to the dynamometer arm using Velcro straps. Participants will be instructed to cross their arms over their chest throughout the test to prevent upper limb involvement ([13](#_ENREF_13)).

Once properly positioned, participants will perform two submaximal voluntary isometric contractions of the knee extensors to familiarize themselves with the testing procedure. These trials will not be recorded. Subsequently, they will practice MVIC trials (without electrical stimulation) until both the investigator and participant are confident that maximal effort is being exerted.

Following familiarization, participants will perform five maximal voluntary isometric contractions (MVIC) of the quadriceps muscle in the extension direction. Each trial will be accompanied by verbal encouragement to ensure maximal effort—participants will be verbally prompted to exert their highest possible force. A minimum rest interval of 60 seconds will be provided between trials to minimize the risk of muscular fatigue during MVIC testing.

The average torque from the five MVIC attempts will be used to quantify quadriceps strength. This procedure will be conducted prior to the tDCS intervention to establish baseline strength values. The same protocol will be repeated following completion of ten tDCS sessions to assess post-intervention changes in muscle strength.

[figure not shown]
.
[figure not shown]

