Quadriceps strength will be assessed using a dynamometer before and after the a-tDCS intervention. Additionally, participants will complete the following validated outcome measures: KOOS (Knee Injury and Osteoarthritis Outcome Score), IKDC (International Knee Documentation Committee), and the Visual Analog Scale (VAS) for pain.

Enhancing quadriceps muscle strength, as a key parameter, may not only help prevent recurrent injuries but also reduce financial burden and alleviate the psychological concerns commonly experienced by patients following ACLR.

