**10.3. Inclusion Criteria**

1. Athletes who are at 2 months post-ACLR surgery at the time of enrollment ([8](#_ENREF_8)).

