**Intervention Protocol**

In the intervention group, participants will receive ten sessions of motor cortex tDCS, administered four times per week. The control group will follow the same schedule, but with sham stimulation. This study will be conducted under a double-blind design, ensuring that both the assessor and participants remain unaware of whether the stimulation is active or sham.

Each physiotherapy session will last 60 minutes and include the following components:

Used to retrain quadriceps muscle activation and enhance strength. Two carbon rubber electrodes (4 × 6 cm), covered with moistened sponge pads, will be placed on the proximal and distal bulk of the quadriceps muscle—one on the vastus lateralis and the other on the vastus medialis. For the hamstring muscle, two similar electrodes will be placed on its proximal and distal bulk (Figure 7).

FES parameters will include trapezoidal pulse currents with 2-second ramp-up and ramp-down times, a pulse duration of 250 microseconds, a frequency of 50 Hz, and a stimulation-to-rest ratio of 1:2 (6 seconds contraction, 12 seconds rest). Stimulation will be applied for 20 minutes per session ([39](#_ENREF_39)), with a maximum intensity of 100 mA ([94](#_ENREF_94)). The physiotherapist will adjust the intensity in each session according to the participant’s tolerance to maximize motor unit recruitment. Participants will be instructed to perform voluntary muscle contractions during the stimulation phase ([103](#_ENREF_103)).

Applied for pain reduction. Two carbon rubber electrodes (4 × 6 cm), covered with moistened sponge pads, will be placed on either side of the knee (Figure 7). TENS will be delivered in conventional mode at a frequency of 100 Hz for 20 minutes per session ([39](#_ENREF_39)).

[figure not shown]

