**13. Ethical and Human Considerations**

1. All stages of the study will respect the cultural beliefs, behaviors, and traditions of the community.

2. Participant information will remain strictly confidential.

3. Honesty and integrity will be upheld during the review and handling of all study documents.

4. A written informed consent form will be signed by all participants.

5. Participants will retain the right to withdraw from the study at any time, for any reason or without providing a reason.

6. Participation in this study will not pose any physical or psychological risk to individuals.

7. Participation will not interfere with participants’ ongoing treatment or daily life activities.

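### The only post-treatment strength and CAR test is triggered by the tenth session, with no visit window and no scheduled test for athletes who stop stimulation early

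*Protocol*

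**What the plan says.** The protocol plans two strength measurements. Section 4 states: "Quadriceps strength will be assessed using a dynamometer before and after the a-tDCS intervention". Section 10.7, under the dynamometer heading, fixes the first: "This procedure will be conducted prior to the tDCS intervention to establish baseline strength values". It fixes the second by an event: the test is "repeated following completion of ten tDCS sessions". CAR comes from the stimulus added during the same dynamometer test, so it shares that trigger.

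The schedule is in the Intervention Protocol: "participants will receive ten sessions of motor cortex tDCS, administered four times per week". For sham it adds: "The control group will follow the same schedule, but with sham stimulation". There is no rule on how missed or late sessions affect the test date.

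Athletes can leave early in two ways. Section 10.5 removes an athlete from the study if pain increases during testing. Section 13 says: "Participants will retain the right to withdraw from the study at any time, for any reason or without providing a reason". Neither provides an outcome visit for someone who does not reach session ten.

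For the questionnaires and VAS, Sections 7.2 and 7.3 speak only of scores before and after stimulation. Section 10.7 schedules only the baseline set.

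**The concern.** A measurement that depends on completing treatment exists only for completers. An athlete who stops at session six never reaches the trigger, and the protocol creates no other occasion to test him. Randomisation protects a comparison of everyone randomised. It does not protect a comparison of those who finished, because finishing happens after randomisation and may be related to arm and to recovery.

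The trigger also leaves elapsed time open. The entry criterion is "Athletes who are at 2 months post-ACLR surgery at the time of enrollment", and both arms receive physiotherapy that includes electrical stimulation of the quadriceps to build strength. The literature review (Section 6, part 4) describes a ten-session trial in ACL injury in which knee extensor strength rose in both arms, the sham-plus-physiotherapy arm included. Strength is therefore expected to rise with time whatever the arm, and an athlete tested later has had more of that rise.

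A statistical analysis plan can choose how to handle missing values. It cannot recover measurements that were never scheduled.

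**Working it through.** The protocol states no final sample size, dropout rate, recovery rate or standard deviation, so there is no figure of its own to reproduce. What can be checked is the schedule, and then how large a bias would be under stated assumptions.

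**Inputs from the protocol**
- Ten sessions at four per week, the same in both arms (Intervention Protocol).
- One baseline test and one repeat after the tenth session (Section 10.7).
- No visit window, maximum interval or later follow-up in the text.

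**Inputs assumed (not in the protocol)**
- Recovery of 1 to 3% of baseline strength per week.
- Dropout of 10% v 10%, 20% v 10% and 30% v 10% (active v sham).
- Stoppers' outcomes 0.5 to 1.0 SD below completers' outcomes.

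**Step 1: time to the tenth session.** Weeks = 10 / sessions per week.
- 4 per week (planned): 10/4 = 2.5 weeks.
- 3 per week: 10/3 = 3.33 weeks, which is 0.83 later.
- 2 per week: 10/2 = 5.0 weeks, which is 2.5 later.

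**Step 2: bias from timing.** Bias = weekly recovery × difference between arms in mean time to test.
- No difference: 0%.
- 0.25 week: 0.25 × (1 to 3%) = 0.25 to 0.75%.
- 1 week: 1 × (1 to 3%) = 1 to 3%.

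Delay shared by both arms cancels from the mean difference. Variation in delay between athletes does not cancel from the spread.

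**Step 3: bias from analysing completers only.** If stoppers lie k SD below completers and a fraction d stops, the completers' mean exceeds the mean of all randomised by d × k. The bias in the difference is (d active − d sham) × k.
- 10% v 10%: 0 × k = 0.
- 20% v 10%: 0.10 × (0.5 to 1.0) = 0.05 to 0.10 SD.
- 30% v 10%: 0.20 × (0.5 to 1.0) = 0.10 to 0.20 SD.

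In these examples the bias favours the active arm, because more of its poorer results go unmeasured. With more stopping in the sham arm the sign reverses.

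**The case against.** The strongest reply is that an end-of-treatment test is a legitimate choice. It holds the number of sessions constant, and the closest ten-session trial cited also measured immediately after treatment. The schedule is the same in both arms, so if it is kept everyone is tested at about 2.5 weeks. The text does not forbid testing early stoppers. The Procedure heading also refers to a flowchart that cannot be seen in the text at hand and might carry visit timing.

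Much of this stands. That stoppers go unmeasured is inferred from the trigger and from silence, not from an explicit exclusion. Keeping to four sessions per week would make the spread in timing small. What does not follow is that an end-of-treatment outcome must depend on completion: the same time point can be set by the date session ten is due.

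Three stronger readings are tempting and are not supported:
- A reader might infer that stoppers lose every outcome. The ten-session condition is attached to the dynamometer test. The questionnaires and VAS are simply not given a post-treatment date.
- A reader might infer that active stimulation is felt far longer than sham, so that unequal dropout is to be expected. The sham section gives how long current flows, not how long it is felt. It describes the sham tingling as similar to active and the current as well tolerated. Unequal stopping is possible, but the protocol gives no evidence for it.
- A reader might set an individual delay of 0.83 to 2.5 weeks, which is 0.8 to 7.5% at 1 to 3% per week, against the 4.9% gain cited in athletes. The first is a shift within one athlete, not a difference between arms. The second is a change from baseline 60 minutes after a single session in healthy female players aged 15 to 17, not an expected effect of ten sessions after reconstruction.

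**Conclusion.** The point holds in limited form. Completion of ten sessions is the only stated trigger for the repeat strength and CAR test. The text gives no visit window and no outcome visit for early stoppers. Followed as written, the strength comparison is one of completers, and late attendance adds recovery-related spread.

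Whether this biases the contrast depends on whether stopping or attendance differs by arm. Sham control and participant blinding make that less likely but do not exclude it. The bias is zero under equality, and the non-zero sizes above rest wholly on the assumed recovery rates, dropout rates and SD gap.

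A related gap belongs with it. The interval between the tenth session and the test is open, while the protocol says excitability changes may last up to 1.5 hours. A same-day test and a test days later could measure different things.

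This should be settled before enrolment, because outcomes not collected on time cannot be collected afterwards.

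**What to change.** In Section 10.7, replace the completion trigger with a date that exists for every randomised athlete. Suggested wording:

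> MVIC, CAR, KOOS, IKDC, ACL-RSI and VAS are repeated in all randomised athletes within a short fixed window [width to be set by the sponsor] around the date on which session ten is due on the planned schedule, about 2.5 weeks after the first session. This applies whatever the number of sessions received and includes athletes who have stopped stimulation, unless consent to follow-up is withdrawn. Sessions received, days from baseline and days since the last session are recorded.

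Keeping the window at the due date preserves an end-of-treatment outcome. A window set well after it would turn the outcome into a short follow-up. Sections 10.5 and 13 need to be reconciled with this text, so that stopping stimulation, leaving the study and withdrawing consent to follow-up are told apart for data collection. If the flowchart shows visit timing, it must agree.

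The change leaves the stimulation and its schedule as they are. It costs a call-back visit for each athlete who stops early. Some athletes will be tested with fewer than ten sessions, and the estimated effect may be slightly smaller because they are included.
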